### Instruments and definitions

The MMSE compiled by Foistein and others in 1975 is one of the most influential and widely used screening scales at home and abroad. The scientific and rationality of this scale in predicting the progress of cognitive function in stroke patients has been fully confirmed. MMSE is a screening scale that mainly evaluates cognitive areas such as orientation, instantaneous memory, calculated attention, delayed recall, ability to understand and use, and language function. This scale is generally used for preliminary screening tests for cognitive function. In clinical practice, the MMSE scale is simple, time-saving, and easy to operate. The scale has high sensitivity and specificity for detecting dementia and has good validity and reliability. However, it also has the disadvantages of rough scores and incomplete evaluation. Because the education level of patients will affect their assessment results, false-positive results may be clinically obtained. Other studies have shown that the MMSE scale scoring method is too simple and leads to poor sensitivity. The sensitivity for screening for mild cognitive impairment (MCI) is only 1–9%, and there is a “ceiling effect”. Therefore, other scales need to be further improved and supplemented.

The Montreal Cognitive Assessment Scale (MoCA) was developed by Canadian Nasreddine and others based on clinical experience and with reference to MMSE (Concise Mental State Examination) cognitive items and scores. The Montreal Cognitive Assessment Scale adds assessments of functions such as executive function, visual spatial function, fluency of words, digital forward and backward. Where MMSE cannot detect cognitive impairment, MOCA can be an effective and simple screening tool. In addition, the patient’s early MOCA score can predict the risk of cognitive impairment and risk in the future and has certain predictive validity. It has certain guiding value for clinical judgment of patients’ cognitive prognosis.

### Safety

Adverse reaction (AE) refers to the occurrence of harmful reactions unrelated to the purpose of treatment during the process of preventing, diagnosing, or treating diseases by applying drugs according to normal usage and dosage. Its specific occurrence condition is to use the medicine in the normal dosage and normal usage and exclude the reaction caused by the drug abuse, excessive misuse, use of the medicine in accordance with the prescribed method, and quality problems. Efficacy indicators reflect the effectiveness of interventions, while adverse events reflect intervention safety. In this study, adverse events refer to adverse medical events that occur after a patient or subject in a clinical trial receive an intervention, but are not necessarily causally related to the intervention. Adverse events and adverse reactions: the concept is different. Adverse reactions are directly related to the intervention, and the scope of adverse events covers adverse reactions.

### Sample size justification

According to clinical experience, the effective rate of PSCI in the intervention group was P1 = 0.80. The PSCI effective rate of the control group was P2 = 0.65 [(two-sided type I error rate of 0.05, *α* = 0.05); (one-sided type I error rate of 0.10, *β* = 0.10)]. Substituting *f* (*α*, *β*) into the formula is as follows: *n*1 = *n*2 = 10.5 × (0.8 × 0.2 + 0.65 × 0.35) ÷ 0.152 = 75.The lost follow-up rate of patients will be controlled at 10%. *n*1 = *n*2 = 83, that is, 83 cases will be taken from each of the intervention group and the control group. According to Cohen, this effect size is considered “moderate”.

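### The sample-size formula gives 181 per arm, not the printed 75; at the planned size, power for 80% versus 65% is about 54% to 59%, not the implied 90%

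*Protocol article*

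**What the plan says.** Under Sample size justification, the protocol article assumes that "the effective rate of PSCI in the intervention group was P1 = 0.80" and that "The PSCI effective rate of the control group was P2 = 0.65". It sets a "two-sided type I error rate of 0.05" and gives beta as 0.10, although it describes beta as a "one-sided type I error rate of 0.10". It takes f(alpha, beta) = 10.5 and evaluates the usual two-proportion formula as "10.5 × (0.8 × 0.2 + 0.65 × 0.35) ÷ 0.152 = 75" per arm. It then allows for 10% loss to follow-up and concludes that "83 cases will be taken from each of the intervention group and the control group", 166 patients in all.

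No other sample-size calculation appears in the article. The Statistical analysis section names the chi-square test for count data.

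**The concern.** The printed expression does not equal the printed result. This matters beyond a misprint because 75 is carried forward: 75/0.9 = 83.3 leads to the 83 per arm that the trial will recruit. If the formula really gives a much larger number, the trial is far smaller than its own assumptions require, and the 10% type II error stated for a 15-point difference is not achieved. A non-significant comparison of response rates could then be read as coming from a 90%-power design when it had little better than an even chance of detecting the assumed effect.

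**Working it through.** **Inputs**, all from Sample size justification: P1 = 0.80, P2 = 0.65, difference 0.15, two-sided alpha 0.05, beta 0.10, f = 10.5, loss 10%, equal arms.

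**Which design the constant fixes.** f = (z for 0.975 + z for 0.90)² = (1.960 + 1.282)² = 10.507. So 10.5 is the constant for two-sided 0.05 and 90% power. The article does not print 90% power, but both beta = 0.10 and f = 10.5 imply it.

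**The article's own formula.** n per arm = f × [P1(1 − P1) + P2(1 − P2)] / (P1 − P2)².

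- Bracket: 0.80 × 0.20 + 0.65 × 0.35 = 0.16 + 0.2275 = 0.3875.
- Divisor: 0.15² = 0.0225.
- Result: 10.5 × 0.3875 / 0.0225 = 180.8, so 181 per arm.
- With 10% loss: 181/0.9 = 201.1, so 202 per arm (201 if the unrounded 180.8 is used).

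**Attempts to reproduce 75.**

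| Reading | n per arm |
|---|---|
| Divisor 0.15² | 180.8 |
| Divisor 0.152 taken literally | 26.8 |
| Divisor 0.15 | 27.1 |
| Pooled-variance formula, same alpha and beta | 185 |
| Same, with continuity correction | 198 |
| Arcsine formula, same alpha and beta | about 183 |
| One-sided 0.05, 90% power | 148 to 150 |
| Two-sided 0.05, 80% power | 136 to 138 |
| One-sided 0.10, 90% power | 114 to 115 |
| One-sided 0.10, 80% power | 78 to 79 |

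The last row comes closest in this table, but the article does not state those settings. With the printed bracket, 75 would need f of about 4.35 (75 × 0.0225 / 0.3875) or a difference of about 0.233 (the square root of 10.5 × 0.3875 / 75). Omitting the control-arm variance term does reproduce it: 10.5 × 0.16 / 0.0225 = 74.7. That is a plausible cause, but only a conjecture, and nothing below depends on it.

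**Power for 80% versus 65%, two-sided 0.05.** Unpooled normal approximation at 75 per arm: SE = √(0.3875/75) = 0.0719; 0.15/0.0719 = 2.087; 2.087 − 1.960 = 0.127; power = Φ(0.127) = 55.0%. Other methods and sizes:

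| Evaluable per arm | Unpooled | Pooled | Exact binomial, chi-square test |
|---|---|---|---|
| 75 | 55.0% | 53.9% | 54.0% |
| 83 | 59.3% | 58.2% | 58.6% |
| 181 | – | – | 89.7% |

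**Detectable difference with 75 per arm and 65% in control.** 90% power is reached at an intervention rate of about 87% (0.869 by normal approximation, 0.871 by exact enumeration), a difference of about 22 points. 80% power is reached at about 84% to 85% (0.844 and 0.846), a difference of 19 to 20 points.

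**The case against.** The arithmetic error itself cannot be defended. The best counter-argument concerns its consequence. The article names the MMSE score as primary outcome and analyses measurement data by t test, rank sum test or MANOVA; it does not define the response rate as an outcome. The 54% is therefore the power of the sizing scenario and not necessarily that of the primary test. As an illustration only, if the standardised mean difference on the MMSE were 0.5 (an assumption; the article gives no SD or mean difference), a two-sided t test would have about 86% power at 75 per arm and 89% at 83. This limits what can be concluded: the trial cannot be said to have 54% power for its primary outcome. It does not rescue the section, because the response-rate calculation is the only support offered for 83 per arm.

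Three smaller points also stand. The 54% assumes that the full 10% is lost, and the figure is about 59% if nobody is. The 90% is implied, not printed. The mislabelling of beta changes no number, since f = 10.5 shows that it was used as the type II error.

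The Study design and setting section refers to a sample-size section in a statistical analysis plan that is not shown. That section may give the calculation in full, but it cannot make the equation printed here correct.

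**Conclusion.** The concern holds. On the stated inputs the formula gives 181 per arm, 2.4 times the printed 75 (181/75), and about 202 per arm after 10% loss against the planned 83 (83/202 = 41%). For the stated target of 80% versus 65%, the planned trial has about 54% power with 75 evaluable per arm and about 59% with all 83, so the type II error is 41% to 46% and not 10%. The only reading involved is that the printed divisor is 0.15 squared, and the other readings do not give 75 either. The power figures assume two-sided 0.05, the chi-square test, independent patients and the article's own rates. They say nothing about power on the MMSE score, which the document does not allow to be computed. The section is wrong as written and must be corrected.

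**What to change.** Correct the Sample size justification section, and the corresponding section of the statistical analysis plan if it repeats the figure:

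- Print the divisor as 0.15² and the result as 181 per arm, about 202 with 10% loss.
- If recruitment stays at 83 per arm, withdraw beta = 0.10 for 80% versus 65%. State instead about 54% power at 75 evaluable per arm (59% if all 83 are evaluable), and a detectable difference of about 22 points at 90% power with 75 per arm and 65% in control.
- Relabel beta as the type II error rate.
- Preferably add the power for the MMSE score at 83 per arm, with the assumed SD and mean difference and their source, since that is the named primary outcome.

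This is a correction of wording and figures. It does not by itself require more patients, which matters because the Trial status section says the study is already in progress. The cost is a less favourable statement of power. Raising recruitment to the size that the formula requires would be a separate decision for the sponsor, at about 119 more patients per arm (202 − 83).

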### Data collection and management

The case report form (CRF) is a paper version, and the CRF is a carbonless copy, in duplicate, to be completed by the investigator. The inspector (CRA) shall conduct an on-site inspection of the CRF, and the problems discovered shall be verified and signed by the researcher after verification. After the completed paper version of the CRF is reviewed and signed by the CRA and the main investigator, the first copy is submitted to the data management unit. After the CRF is submitted, a logical data review is performed by the data management team. If there is any doubt about the data, the data administrator will send an “electronic data inquiry” to the CRA and the researcher and send the inquiry to the researcher through the CRA. The researcher should answer and return as soon as possible. All error content and modification results shall be recorded and kept properly. Paper CRFs should be properly recorded and kept between researchers, CRAs, and data stewards.

### Statistical analysis

Statistical analysis will be performed using SPSS 25.0 software for statistical analysis. The normality of the measurement data is tested. The data obeying the normal distribution is Student’s *t* test, which is expressed by mean ± standard deviation. The data not obeying the normal distribution is rank sum test and marginal homogeneity test. Count data are expressed by rate and composition ratio, and comparison is performed by chi-square test. Repeated measurement data are expressed by mean ± standard deviation, intra-group comparison is performed by analysis of variance of repeated measurement data, and inter-group comparison is by multivariate analysis of variance (MANOVA). *P* ≤ 0.05 indicates that the difference is statistically significant.

### Ethics and dissemination

This study has been approved by the Ethics Committee of Dongzhimen Hospital Affiliated to Beijing University of Chinese Medicine (reference number DZMEC-KY-2019-26). Independent clinicians and biostatisticians with extensive research experience in clinical trials will serve as the Data and Safety Monitoring Committee. The Ethics Committee of Dongzhimen Hospital Office may perform random audits to ensure that relevant regulations and guidelines are met. Study participation is voluntary and can be discontinued at any time, and deciding not to take part will not affect a patient’s care. Protocol amendments, adverse effects reporting, and annual review will be overseen by the Ethics Committee of Dongzhimen Hospital. The information provided by the patients will only be shared with members of the research team. Every effort will be made to keep patient information confidential. All research-related paper documents will be kept in a locked cabinet. All patient information will be kept strictly confidential.

## Trial status

Approval documents: the vision of study protocol (V1.0, 2018.12.20), informed consent (V2.0, 2019.03.26), case report form, recruitment advertisement, and copy of the main researcher GCP training certificate. At the time of submission of the manuscript, the study is in progress. We expect to complete the recruitment of subjects on December 31 of the same year.

## Data Availability

Not applicable.

## Abbreviations

AE: Adverse reaction
CRF: Case report form
MANOVA: Multivariate analysis of variance
MOCA: Montreal Cognitive Assessment Scale
MBI: Modified Barthel Index Rating Scale
MCI: Mild cognitive impairment
MMSE: Mini Mental State Examination Scale
PSCI: Post-stroke cognitive impairment
PRECIS-2: Pragmatic Explanatory Continuum Indicator Summary Framework-2 Recommendations for Interventional Trials
SOP: Standard operation procedures
SS-QOL: Stroke-specific quality of life scale
SPIRIT: Standard Protocol Items: Recommendations for Interventional Trials
TCM: Traditional Chinese medicine
